### Intervention Fidelity and Adherence Monitoring

Several measures are implemented to ensure intervention fidelity and to monitor participant adherence. Daily listening compliance is tracked automatically through the custom-developed mobile app, which records session initiation time, duration of playback, and completion status for each listening session. Adequate adherence is defined a priori as completion of at least 80% of scheduled listening sessions (ie, a minimum of 45 of 56 daily sessions over the 8-week intervention period). Participants falling below this threshold will be classified as nonadherent for the purpose of per-protocol analysis, although all randomized participants will be included in the primary intention-to-treat analysis regardless of adherence level. To ensure the quality and consistency of AI-generated music in the IMT arm, a 2-stage quality assurance process is used. First, all generated tracks are screened against predefined acoustic parameters (as described above) to exclude those falling outside acceptable ranges. Second, a certified music therapist reviews a random sample of generated tracks each week (approximately 20% of total output) to verify that the musical content is therapeutically appropriate, free of unexpected artifacts, and consistent with the intended affective trajectory. Any quality concerns are flagged and addressed before participant delivery. For the nonindividualized arm, intervention fidelity is maintained using a standardized track library curated by the same certified music therapist, with track selection following the predefined affective trajectory protocols. Session delivery is identical across both arms in terms of duration, frequency, and environmental instructions.

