
### Interventions

#### Nonindividualized Receptive Music Therapy

Participants engage in daily 30-minute instrumental listening sessions curated by a certified music therapist. The music therapists hold a master’s degree or higher in music therapy with a minimum of 5 years of clinical experience in psychiatric settings. Track selection follows a standardized protocol based on the predefined affective trajectory framework (Figure 2), and the final track list for each participant is reviewed by a second member of the research team to verify adherence to the selection criteria. Selection adheres to the “ISO principle” of mood entrainment [35]. Music initially matches the participant’s current affect and gradually shifts toward an adaptive target state. Before treatment, participants complete the Short Test of Music Preferences-Revised (STOMP-R), which assesses liking for 23 musical styles grouped into 4 categories on a 1‐7 scale (1=dislike strongly; 7=like strongly) [36,37]. Based on prior site-specific data showing high preference for “Reflective & Complex” and “Upbeat & Conventional” styles, the therapist selects instrumental tracks while excluding lyrical content to minimize semantic processing. Each session comprises 6 to 10 excerpts ordered to follow a specific affective trajectory: (1) for MDD and GAD: The sequence guides affect upward (eg, calm and sad → warm → cheerful → relaxed; Figure 2A); (2) for PI: The sequence follows a biphasic trajectory. It initially elevates affect to reduce negative rumination, then progressively decreases tempo and complexity to facilitate sleep onset (Figure 2B).

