**Figure 2. F2:**
[figure not shown]
Music affective trajectories used in nonindividualized receptive music therapy (**A**) Affective trajectory for participants with major depressive disorder or generalized anxiety disorder, showing a gradual upward shift in target emotional valence (low → higher → moderate and settled) across the 30-minute session. The x-axis represents session time (minutes 0‐30); the y-axis represents target arousal and valence level on a standardized scale (higher score indicates higher arousal and positive valence). (**B**) Biphasic affective trajectory for participants with primary insomnia (PI) showing a biphasic trajectory. The x-axis represents session time (minutes 0‐30); the y-axis represents target arousal level (higher score indicates higher arousal and positive valence). The trajectory features a gentle initial rise in affect to reduce negative cognitions, followed by a progressive taper (slower tempo, simplified rhythm and melody, increased repetition) to lower physiological arousal before sleep.

In addition to the listening intervention, participants in the nonindividualized arm complete a brief weekly music-experience questionnaire that mirrors the contact time and structure of the weekly preference assessment used in the IMT arm. This questionnaire records the participant’s listening experience, mood, and engagement but is not used to alter the curated track list; its purpose is to equate the 2 arms for participant–researcher contact and procedural engagement, thereby reducing differential attention and expectation effects.

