#### IMT

IMT uses an artificial intelligence (AI)–enabled pipeline to tailor the interventions to weekly patient preferences. Before each week’s session, participants complete a preference questionnaire across 6 dimensions: emotion, style, intensity, instrumentation, variation, and tempo. These inputs are converted into standardized prompts for the Suno music platform (V4 model; API: sunoapi.org). For example, a selection of “calm, Western Classical, flute and piano and cello, slow tempo” is programmatically rendered into a specific generation prompt. The system generates 16 unique instrumental tracks, which the participant rates on a 1‐7 scale. The 8 highest-rated tracks are compiled into the 30-minute intervention set for that week. To ensure therapeutic consistency across participants, the AI-generated tracks are subject to predefined acoustic constraints. All generated tracks are required to be purely instrumental (lyrical content is excluded). Furthermore, key acoustic features, including tempo (beats per minute), spectral centroid, and rhythmic complexity, are logged for each generated track. The therapeutic structure of the IMT condition mirrors that of the nonindividualized arm in session duration (30 min daily), number of tracks per session (6 to 10 excerpts), and overall affective trajectory framework. The sole difference lies in the source of the musical material (AI-generated based on individual preferences vs therapist-curated from existing libraries). Participants are instructed to listen once daily in a quiet environment and to focus their attention on the auditory experience and the emotions it evokes. The playback interface displays the following guidance: “Please adjust your posture to feel relaxed and comfortable. Close your eyes and begin deep breathing. After the music begins, focus all your attention on the music and the feelings it evokes.”

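### The therapist check on IMT music samples single generated tracks, so it reaches about 20% of delivered tracks and cannot show whether the compiled session follows the affective trajectory

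*Protocol article*

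**What the plan says.** The IMT section sets out the weekly production steps. Each participant states preferences on six dimensions, and these become a generation prompt. "The system generates 16 unique instrumental tracks, which the participant rates on a" seven-point scale, and "The 8 highest-rated tracks are compiled into the 30-minute intervention set for that week". The same section says that IMT mirrors the other arm in session length, number of tracks and affective trajectory framework, and concludes: "The sole difference lies in the source of the musical material".

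Intervention Fidelity and Adherence Monitoring describes two quality stages. First, every generated track is screened on acoustic parameters. Second, "a certified music therapist reviews a random sample of generated tracks each week (approximately 20% of total output"), to confirm that the content is suitable, "free of unexpected artifacts, and consistent with the intended affective trajectory". It adds: "Any quality concerns are flagged and addressed before participant delivery".

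The trajectory itself is defined for the comparator arm, under Nonindividualized Receptive Music Therapy: "Each session comprises 6 to 10 excerpts ordered to follow a specific affective trajectory". The Figure 2 legend plots it over minutes 0 to 30. For MDD and GAD it is described as "showing a gradual upward shift in target emotional valence (low → higher → moderate and settled) across the 30-minute session". For insomnia it is an early rise followed by a taper in tempo and complexity. In that arm a second team member reviews every participant's final list against the selection criteria.

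**The concern.** The stated purpose and the stated sampling unit do not match. A trajectory belongs to an ordered set of tracks. The therapist is given tracks drawn singly from everything generated, half of which never enter a set. The reviewer can judge whether a track has artifacts or an unsuitable mood, but not whether the eight tracks, played in order, follow the intended path.

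This matters for what study 3 can conclude. Primary Outcome Analysis treats the contrast as informative about personalization of the stimulus, and the heterogeneity section uses trajectory type, which is tied to diagnosis, as a sensitivity covariate. Both presuppose that the two arms receive the same trajectory. The production steps the article states for IMT are one weekly preference prompt and then selection by liking, and these do not by themselves create an ordering. If the ordering is absent or weak in IMT, study 3 compares trajectory-guided music with preference-selected music, and the difference between arms is wider than the source of the material.

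**Working it through.** The 20% is a design choice, so there is no derived figure to reproduce. The check is coverage arithmetic followed by a comparison of the sections.

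**Inputs.** From the IMT section: 16 tracks generated and 8 delivered per participant-week. From Intervention Fidelity and Adherence Monitoring: about 20% of generated tracks reviewed. From Table 1: 300 participants randomized 1:1 (150 in IMT) for 8 weeks. Assumptions: sampling is independent of the ratings, and retention is complete.

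**1. Coverage per participant-week**
- Reviewed: 16 × 0.20 = 3.2 tracks.
- Outside the set: (16 − 8)/16 = 50%.
- Delivered and reviewed: 8 × 0.20 = 1.6. Delivered and not reviewed: 8 × 0.80 = 6.4 (80%).
- The 80% comes from the 20% fraction alone. The unused half does not change it, but it means about half the effort (1.6 of 3.2 reviews) falls on tracks outside any set.

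**2. Weekly sets with no therapist-reviewed track**
- Independent 20% sampling: 0.8^8 = 16.8%.
- Exactly 3 of 16 drawn: C(8,3)/C(16,3) = 56/560 = 10.0%.
- Exactly 4 of 16 drawn: C(8,4)/C(16,4) = 70/1,820 = 3.8%.

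**3. Study 3 totals**
- Sets: 150 × 8 = 1,200.
- Generated: 1,200 × 16 = 19,200. Reviewed: 19,200 × 0.20 = 3,840.
- Delivered: 1,200 × 8 = 9,600. Of these, 9,600 × 0.20 = 1,920 are reviewed and 7,680 are not.

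**4. Same workload drawn from the delivered set**
- Coverage: 3.2/8 = 40%, or 3,840 of 9,600.
- Sets with no reviewed track: 0.6^8 = 1.7%.

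**5. Side by side**

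| | Nonindividualized arm | IMT arm |
|---|---|---|
| How the set is formed | Therapist orders excerpts along the trajectory | Top 8 by participant rating; no ordering step stated |
| Unit of human review | Final list | Single generated track |
| Extent of human review | Every participant | About 20% of generated tracks |
| Can the review see order? | Yes | No |

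The last row carries the point. It does not depend on the sampling fraction: a larger random sample of unordered single tracks would still not show the order.

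**The case against.** The strongest reply is that sampling generated output is a legitimate process check. All 16 tracks in a week come from one participant's weekly preferences, so a fault in the prompt would tend to show in any of them, delivered or not. The chance that at least one of the 16 is sampled is 1 − 0.8^16 = 97%. Participants also hear all 16 while rating, so reviewing the other eight is not wasted. This stands. A reader might infer that music plainly unsuited to a participant would usually pass unseen, and the documents do not support that.

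A reader might also infer that 80% of delivered music is unchecked. It is not: the automated screen covers every track, and the 80% refers to therapist review only.

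Third, this is a condensed article, and an ordering step for IMT may sit in the full protocol. That also stands. It rules out saying that IMT sets lack a trajectory or that the equivalence statement is false. It does not answer the mismatch, because the article itself gives the unit of review and says what that review verifies, and the one cannot deliver the other.

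**Conclusion.** The point holds in a limited form. The therapist check reaches about 20% of delivered tracks (19% if exactly 3 of 16 are drawn, 25% if exactly 4), and its unit cannot show the session-level trajectory it is said to verify. The assurance that concerns are dealt with before delivery can apply only to sampled tracks and to those the acoustic screen rejects. The statement that the arms differ only in source is unverified, which is not the same as shown to be wrong.

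The coverage figures assume sampling independent of the ratings. The article does not say whether review comes before or after rating. If every sampled track happened to be one later selected, coverage would be 40%. The study 3 totals also assume full retention. The mismatch of unit depends on neither assumption. It is worth correcting because it bears on how the randomized contrast is interpreted and because the correction is cheap.

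**What to change.** 1. After rating and before release, run an automated check on every compiled, ordered set against the protocol's own trajectory for that diagnosis, using the features already logged. Tempo and rhythmic complexity can test the insomnia taper, which the Figure 2 legend describes partly in those terms. The MDD and GAD path is one of valence, which the logged features are not shown to measure, so it needs therapist judgement on flagged or sampled sets.

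2. Draw the existing therapist workload, about 3.2 tracks per participant-week, from the delivered set and show each track with its position. Coverage of delivered tracks rises from about 20% to 40%, and sets with no reviewed track fall from about 17% to about 2%. A prompt-level fault would be sampled about as often as now (1 − 0.6^8 = 98%, against 97%).

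3. If the trajectory is not enforced in IMT, reconcile the IMT and fidelity sections by withdrawing the statements that IMT mirrors the trajectory framework and that source is the only difference.

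Cost: a short script and some protocol wording, with no more sampled tracks for the therapist to review; flagged MDD and GAD sets should be taken within that workload. The downside is that review must fit between rating and release, and tracks heard only during rating get the automated screen alone.

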### Study Procedure and Data Collection

Recruitment occurs at Peking Union Medical College Hospital through clinician referrals and community outreach. Following screening and provision of written informed consent, participants are assigned a unique alphanumeric study code (eg, IMT-1‐001). Eligible participants receive training on a custom-developed mobile app, which serves as the platform for collecting patient-reported outcomes and for delivering the daily musical intervention. Data acquisition encompasses six primary domains:

Demographics and history: age, sex, education, and detailed medical and psychiatric historySymptom severity: assessed using the Montgomery-Åsberg Depression Rating Scale (MADRS), Hamilton Anxiety Rating Scale (HAMA), Pittsburgh Sleep Quality Index (PSQI), Clinical Global Impression–Severity (CGI-S), and Immediate Mood Scale (IMS)Psychosocial functioning: evaluated via the Unified Psychophysiological-Psychosocial Assessment Questionnaire (UPPSAQ-70), Defense Style Questionnaire (DSQ), and Toronto Alexithymia Scale (TAS), etcNeurophysiology: includes optional assessments such as electroencephalography (EEG), functional near-infrared spectroscopy (fNIRS), MRI, and heart rate variability (HRV)Treatment credibility and expectancy: assessed at baseline (after allocation, before the first session) in studies 2 and 3 using the CEQ to permit measurement and statistical adjustment for expectation effectsSafety: monitored using the Young Mania Rating Scale (YMRS), the Brief Psychiatric Rating Scale (BPRS-4) positive symptom subscale, the UKU Side Effect Rating Scale, the Frequency, Intensity, and Burden of Side Effects Rating (FIBSER), and the Columbia-Suicide Severity Rating Scale (C-SSRS)

Follow-up visits occur at weeks 1, 2, 4, 6, and 8. These assessments focus on symptom severity, neurophysiology, and safety. At baseline in studies 2 and 3, participants additionally complete the Short Test of Music Preferences-Revised (STOMP-R). In study 4, baseline procedures include the application of the treatment-response prediction model derived from earlier datasets. For participants undergoing EEG, protocols include resting-state, P300, and mismatch negativity (MMN) paradigms. Additionally, a music-stimulation task (approximately 20 min of curated excerpts) is conducted at baseline and week 8 to characterize neural reactivity to the intervention.

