**Methods:**

This multistage research program is being conducted at Peking Union Medical College Hospital and comprises four sequential studies: (1) a cross-sectional pilot study (n=20) to benchmark clinical and electroencephalography features, (2) a prospective cohort study (n=80) evaluating the efficacy and safety of nonindividualized receptive music therapy, (3) a pilot randomized clinical trial (n=300) comparing nonindividualized therapy with IMT over 8 weeks, and (4) a prospective validation study (n=60) of a treatment-response prediction model. Participants include adults aged 18 to 60 years with mild-to-moderate major depressive disorder, generalized anxiety disorder, or primary insomnia, along with healthy controls. In the nonindividualized arm, participants engage in daily 30-minute listening sessions using therapist-curated instrumental tracks designed to regulate mood. In the IMT arm, an AI generation pipeline creates bespoke instrumental tracks based on weekly participant preferences regarding tempo, instrumentation, and emotional valence. To equalize participant–researcher contact across arms and reduce attention and expectation bias, participants in the nonindividualized arm complete a weekly music-experience questionnaire matched in length and timing to the IMT arm’s weekly preference assessment, and treatment credibility and outcome expectancy are measured at baseline in both arms. The primary outcomes are the response rate at 8 weeks (defined as ≥50% reduction in Montgomery-Åsberg Depression Rating Scale [MADRS], Hamilton Anxiety Rating Scale [HAMA], or Pittsburgh Sleep Quality Index [PSQI] scores) and changes in quantitative electroencephalography characteristics. Secondary outcomes include changes in MADRS, HAMA, and PSQI scores from baseline to 8 weeks.

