Study 4 (Prediction Validation)	A prospective cohort study (n=60) in which all participants receive IMT, and the prespecified prediction model derived from studies 1‐3 is applied at baseline to classify participants as predicted responders or nonresponders.	Validates the prediction model in an independent sample. Unlike study 2, which evaluates the nonindividualized intervention, study 4 exclusively administers IMT and focuses on predictive accuracy rather than treatment efficacy.

a MDD: major depressive disorder.

b GAD: generalized anxiety disorder.

c PI: primary insomnia.

d HC: healthy control.

e EEG: electroencephalography.

f RCT: randomized clinical trial.

g IMT: individualized (receptive) music therapy.

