### Treatment-Response Prediction Model

The treatment-response prediction model to be validated in study 4 will be developed using data from studies 1 through 3. Candidate predictors will include baseline demographic characteristics (age, sex, and education), clinical variables (baseline symptom severity scores, disorder diagnosis, duration of illness, and medication status), music preference profiles (STOMP-R scores), and baseline neurophysiological features (resting-state EEG spectral power and frontal alpha asymmetry). The outcome variable for model development will be treatment response at 8 weeks, defined as a reduction of 50% or greater in the disorder-specific primary outcome measure. Model development will use logistic regression with regularization (elastic net) to handle the potentially large number of candidate predictors relative to the sample size, with internal validation using 10-fold cross-validation. The final model will be prespecified and locked before its application to the study 4 validation cohort. Model performance in study 4 will be assessed using discrimination metrics (area under the receiver operating characteristic curve, sensitivity, and specificity) and calibration measures (Hosmer–Lemeshow test and calibration plots). Should the cumulative sample from studies 1 through 3 prove insufficient for robust model development, alternative approaches such as penalized regression or decision-tree methods will be considered, and the model validation in study 4 will be framed accordingly. A detailed statistical analysis plan for the prediction model will be finalized before study 4 enrollment commences.

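### The model locked for study 4 may contain STOMP-R or EEG terms that study 4 is not clearly scheduled to collect, and its Hosmer-Lemeshow check is weak at n=60

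*Protocol article*

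**What the plan says.** The abstract describes study 4 as "a prospective validation study (n=60) of a treatment-response prediction model". Table 1 (Study Design) says that all its participants receive IMT and that the model "is applied at baseline to classify participants as predicted responders or nonresponders".

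The Treatment-Response Prediction Model section lists the candidate predictors, among them "music preference profiles (STOMP-R scores), and baseline neurophysiological features". The model is fitted by elastic-net logistic regression on studies 1 to 3 and locked before use in study 4. "Model performance in study 4 will be assessed using discrimination metrics", together with a Hosmer-Lemeshow test and calibration plots. If the development sample proves too small, "alternative approaches such as penalized regression or decision-tree methods will be considered". A separate analysis plan for the model is to be finalised before study 4 enrolment.

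On collection, Study Procedure and Data Collection says: "At baseline in studies 2 and 3, participants additionally complete the Short Test of Music Preferences-Revised (STOMP-R". Its next sentence turns to study 4: "In study 4, baseline procedures include the application of the treatment-response prediction model derived from earlier datasets". The same section counts EEG among optional assessments. Study Design places EEG in the framework shared by all studies, and Comparison With Prior Work says that it runs through the whole program.

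**The concern.** Study 4 exists to measure predictive accuracy. A locked model can be scored only for people in whom every retained predictor was measured. If STOMP-R is retained and not collected, nobody can be scored without altering the model or imputing a variable that is wholly absent from the cohort. If EEG is retained and only some participants have it, validation falls on a self-selected part of an already small sample. A later analysis plan cannot recover a baseline measure that was never taken.

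The second issue is whether the calibration test can show the error most likely to occur. The model is trained partly on patients given nonindividualized therapy, lists no treatment term, and is then applied to patients who all receive IMT. If IMT works as hypothesised, the model will predict too few responders.

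**Working it through.** **Step 1: predictors against schedule.**

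| Predictor | Candidate for the model? | Scheduled in study 4? |
|---|---|---|
| STOMP-R scores | Yes (Treatment-Response Prediction Model) | Not named. Listed at baseline of studies 2 and 3. The intervention text describes it only under nonindividualized therapy, which study 4 does not give. |
| Resting EEG power, frontal alpha asymmetry | Yes (same section) | Contradictory: optional in Study Procedure and Data Collection; in all studies in Study Design and Comparison With Prior Work. |

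The IMT section has its own weekly questionnaire with 6 dimensions. It is a different instrument and cannot supply STOMP-R scores, which rate 23 styles.

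**Step 2: expected direction of miscalibration.** The article gives no sample-size or precision figure for study 4, so there is none to reproduce. The inputs below are assumptions taken from the Sample Size Calculation section: 70% response on nonindividualized therapy, and an IMT benefit equal to the 20-point threshold, giving 90%. Development patients with an 8-week response are 60 from study 2 (20 each of MDD, GAD and PI) plus 150 per arm from study 3. Study 1 is cross-sectional and has no treatment response.

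- Nonindividualized: 60 + 150 = 210. IMT: 150. Total: 360.
- Average prediction without a treatment term: (210 × 0.70 + 150 × 0.90) / 360 = (147 + 135) / 360 = 78.3%.
- Study 4 truth on the same assumptions: 90%, so under-prediction of 90 − 78.3 = 11.7 points.

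**Step 3: power of the Hosmer-Lemeshow test, n=60.** Simulation with a normal linear predictor (SD 0.9, AUC about 0.73), 10 equal risk groups of 6, two-sided alpha 0.05. The statistic is the sum over groups of (O − E)² / [E(1 − E/n_g)]. The comparator, calibration-in-the-large, is z = (Σy − Σp) / √Σp(1 − p).

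| Predicted / true response | HL, 10 df | HL, 8 df | Calibration-in-the-large |
|---|---|---|---|
| 78.3% / 90% | about 2% | about 8% | about 70% |
| 78.3% / 66.6% | about 47% | about 60% | – |
| Calibrated | about 6% | about 12% | – |

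In the first row the test flags the miscalibrated model less often than a correct one. With 5 groups and 5 df it rejects in about 17%.

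**Step 4: other departures.** Linear predictor SD 1, predicted response 70%, 10 groups, 10 df:

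- calibration slope 0.7: 12%; slope 0.5: 22%
- about 7 points over-prediction: 18%; about 8 points under-prediction: 3.5%
- about 17 points over-prediction: 62%; no predictive value (slope 0): 71%

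At 50% predicted response, slopes of 0.7 and 0.5 give 14% and 27%, and shifts of 8 to 10 points give 9% to 13%.

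**Step 5: fallback.** Elastic net is a form of penalized regression. Offering penalized regression in case elastic net proves inadequate changes nothing.

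**The case against.** A reader might infer that study 4 cannot score its model at all. The article does not support that. STOMP-R and EEG are candidates only, elastic net may drop them, and the listed study 4 baseline procedures are introduced as inclusions rather than a full list. The promised model plan is due before study 4 enrolment, so the gap can still be closed in time. What stands is that no section schedules STOMP-R in study 4, while the model may need it.

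A reader might also take EEG as settled to be optional. Two other sections say the opposite, so the finding is a contradiction.

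On calibration, the strongest objection is that the 2% to 8% figure belongs to one scenario, in the direction where the test is weakest, with an assumed number of groups. This is correct. A general claim of almost no power fails against the 47%, 62% and 71% above. A claim that the chi-square approximation breaks down fails too: with 10 df, which suits a fixed external model, the false-positive rate is about 6%. The inflation to about 12% appears with 8 df, and the article does not state the df.

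Calibration plots, AUC, sensitivity and specificity are also planned, and nowhere does the article say that a non-significant test will be taken as good calibration. The weakness of the test remains, as does the fact that under-prediction is the error implied by the trial's own hypothesis.

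The decision-tree half of the fallback is not criticised here, because nothing in the article shows that trees would do worse.

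**Conclusion.** The concern holds in a conditional form. STOMP-R is a candidate predictor with no scheduled collection in the one study where the locked model must be scored. EEG is described both as optional and as universal. The consequence depends on what the model retains: a STOMP-R term would stop scoring for everyone as scheduled, and an EEG term would stop it for anyone without EEG.

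The Hosmer-Lemeshow test at n=60 has low power for single mild-to-moderate departures (about 4% to 27% with 10 groups and 10 df) and is weakest for under-prediction. The contrast of about 2% to 8% with about 70% rests on 10 groups, 70% response on nonindividualized therapy, a 20-point IMT benefit and a linear predictor SD of 0.9. The article gives the 70% and the 20 points for planning study 3; applying them to study 4 is an assumption. The fallback wording is a small but plain error.

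**What to change.** 1. Add STOMP-R to the study 4 baseline in Study Procedure and Data Collection.
2. Reconcile that section with Study Design and Comparison With Prior Work on whether EEG is optional. Unless baseline resting EEG is required in study 4, lock a primary model without EEG terms and report the model with EEG as secondary.
3. Replace the Hosmer-Lemeshow test with calibration-in-the-large and calibration slope, each with a 95% CI, and keep the planned calibration plot.
4. In the fallback, replace penalized regression with a smaller, prespecified predictor set.

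The cost is one short questionnaire per study 4 participant, some analysis wording, and possibly the loss of EEG terms from the primary model. All of it can be settled before study 4 enrolment, when the model's analysis plan is due.
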